## Materials and equipment

2

### Methods

2.1

#### Ethics and study design

2.1.1

This prospective study has been reviewed and approved by the Research Ethics Board of the Centre Intégré Universitaire de Santé et des Services Sociaux du Nord-de-l’Île-de-Montréal (CIUSSS-NIM; MP-12-2022-2984) and Centre Intégré Universitaire de Santé et des Services Sociaux de l’Est-de-l’Île-de-Montréal (CIUSSS-EST; MEO-12-2023-2472). Data will be collected at the Hôpital Maisonneuve-Rosemont (CIUSSS-EST, Montreal, Canada) and Hôpital du Sacré-Cœur-de-Montréal (CIUSSS-NIM, Montreal, Canada).

#### Participants

2.1.2

Using a within-subject study design, this study will enroll 30 neurologically healthy patients scheduled for elective surgery under GA. The sample size is justified based on feasibility, prior literature, and the within-subject design of the study. Patients will be included if they are aged 18–80 years, comprehend French or English, have an American Society of Anesthesiology (ASA) score of I to III, and are scheduled for major elective surgery (abdominal, gynecologic, urologic, thoracic, or orthopedic) requiring more than 60 min of GA. Patients will be excluded for unstable coronary pathology, heart rhythm disorder, emergency or brain surgery, pregnancy, preoperative hemodynamic failure, substance use disorder (alcohol, drugs, opioids as defined by the DSM-V) in the last 3 months, daily use of opioids in the last 7 days, chronic pain conditions, severe psychiatric pathologies, or epilepsy.

Patients will be contacted by phone within 7 days prior to their surgery by a member of the study team who is not a member of the patient’s treating team. Details of the study will be explained to them, and all questions answered by a member of the study team, who will also verify inclusion/exclusion criteria. The information and consent form, as well as an illustrative document explaining study procedures, will be sent to eligible patients by email. The morning of the surgery, a member of the research team will meet the patients to address any concerns and written informed consent will be obtained.

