The effectiveness of this technique relies on the intact transmission of auditory signals through the peripheral and central auditory pathways, beginning with cochlear activation and propagation via the vestibulocochlear nerve (cranial nerve VIII) to higher-order cortical regions (Bellesi et al., 2014; Esfahani et al., 2023; Ngo et al., 2013). Studies suggest that these signals ascend predominantly through the non-lemniscal pathway and reach higher-order associative regions, where they evoke event-related potentials in response to sound (Atienza et al., 2001; Hu, 2003; Jourde et al., 2023). Previous EEG and fMRI studies have confirmed that the brain retains its ability to process auditory stimuli during deep states of anesthesia (Hartikainen and Rorarius, 1999; Nourski et al., 2017; Plourde et al., 2006). These findings suggest that the necessary sensory and cortical pathways required for CLAS remain functional under anesthesia, providing a neurophysiological basis for exploring whether CLAS can effectively modulate anesthetized brain states.

Auditory stimulation is particularly well suited for closed-loop modulation of SOs under anesthesia for several reasons: auditory stimulation at low intensity offers a simple, non-invasive, and temporally precise approach for engaging slow oscillatory dynamics, with minimal interference with the surgical field. In sleep, auditory stimuli are well known to evoke K-complex–like responses that share core morphological and generative features with SOs and rely on corticothalamic circuitry involved in *δ*-wave generation (Cash et al., 2009; Colrain, 2005). Under propofol anesthesia, early auditory cortical responses and thalamocortical relay activity are suppressed but not abolished, providing a preserved pathway through which phase-locked auditory input may interact with drug-stabilized δ oscillations. This preserved auditory–corticothalamic coupling provides a mechanistic rationale for using auditory stimulation, rather than other sensory modalities, to probe and modulate slow oscillatory activity under general anesthesia (Ngo et al., 2013; Nourski et al., 2017).

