#### Auditory stimuli

2.1.5

The auditory stimuli are composed of binaural bursts of pink noise, also known as 1/f noise. The auditory stimuli last for 50 ms, with a 5 ms rising and falling slope respectively, and are delivered through a trigger box connected to the CLAS detection algorithm. Sound volume will be set at a maximum of 65 dB SPL at the ear canal (Henin et al., 2019).

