## Limitations

6

Several limitations should be acknowledged. First, the study design is restricted to neurologically healthy surgical patients, which may limit generalizability to vulnerable populations, where anesthetic management is most challenging. Second, the inclusion of a broad age range (18–80 years) was necessary to facilitate recruitment in a clinical intraoperative setting but may introduce age-related neurophysiological and pharmacokinetic variability. To mitigate this, the study employs a within-subject design and includes age as a covariate in statistical analyses; if sampling permits, this cohort may also enable exploratory analyses of age-related differences in CLAS responsiveness under anesthesia. Third, although high-density EEG offers improved spatial resolution compared to standard EEG, source localization remains constrained by the absence of individual MRI head models; therefore, source localization and propagation findings should be interpreted cautiously (Custo et al., 2017). This reflects a feasibility-driven decision, as requiring an additional MRI visit in a surgical population would substantially increase participant burden and limit recruitment; future studies may incorporate individual MRI to enable more precise localization. Fourth, auditory stimuli may be variably attenuated by earphones and earmuffs, and inter-individual differences in auditory sensitivity under anesthesia could influence responsiveness to CLAS. Finally, the protocol focuses on short stimulation blocks and acute nociceptive challenges; the long-term impact of CLAS on anesthetic requirements, recovery profiles, or postoperative outcomes remains untested.

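### The stated eligibility criteria admit patients with known hearing loss to a trial of a sound-based intervention, which would dilute the Part 1 contrasts between in-phase, anti-phase and sham.

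*Protocol article*

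**What the plan says.** Section 2.1.2 (Participants) sets the population: "this study will enroll 30 neurologically healthy patients scheduled for elective surgery under GA". On age and language it says: "Patients will be included if they are aged 18–80 years, comprehend French or English". It adds ASA class and type of surgery. The exclusion list begins "Patients will be excluded for unstable coronary pathology, heart rhythm disorder, emergency or brain surgery, pregnancy" and ends with "daily use of opioids in the last 7 days, chronic pain conditions, severe psychiatric pathologies, or epilepsy". Nothing in it concerns hearing, hearing aids or the ear. Screening is by telephone, and the listed criteria are verified in that call.

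Section 1.5 states the premise of the intervention: "The effectiveness of this technique relies on the intact transmission of auditory signals through the peripheral and central auditory pathways". Section 2.1.5 fixes the level: "Sound volume will be set at a maximum of 65 dB SPL at the ear canal". It describes no adjustment to the individual's threshold. Section 2.2.2 delivers the sound to both ears through in-ear earphones worn under earmuffs.

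Section 6 (Limitations) concedes that earphones and earmuffs may attenuate the sound variably and that "inter-individual differences in auditory sensitivity under anesthesia could influence responsiveness to CLAS". It attaches no screening, measurement or analysis to that remark. The covariates named in sections 3.7.1 and 3.7.3 are age and sex.

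**The concern.** The intervention is a sound, so a patient whose ears do not transmit it has not received the intervention, whatever the software triggers. The article treats intact transmission as a condition for the technique to work, but its criteria do not ask for it, in a population that reaches age 80.

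The within-subject design gives no protection. A patient who does not receive the sound contributes a true in-phase minus sham difference near zero, and likewise for anti-phase. This pulls the mean effect towards zero and adds between-patient spread. Age as a covariate does not repair it, because an age main effect does not model a difference between conditions that depends on hearing.

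Two readings of the results are at stake. Section 4 describes this as the first protocol to apply CLAS during general anesthesia, so a null or weak result will need explaining, and unidentified non-reception would be one competing explanation. Section 6 also raises exploratory analyses of age and CLAS responsiveness; without hearing status, age-related hearing loss would be mixed into any such pattern.

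**Working it through.** **1. The plan's own figure.** The sample size is 30, and the article says: "The sample size is justified based on feasibility, prior literature, and the within-subject design of the study". It gives no effect size, standard deviation, alpha or power, so 30 cannot be reproduced and no stated power margin exists against which to set a loss.

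**2. Which comparisons are exposed.**
- Part 1 (SA1 and SA2): in-phase, anti-phase and sham blocks are compared on delta-wave, BIS and network outcomes. A patient who does not receive the sound has little or no true difference between any two blocks, so these contrasts are diluted.
- Part 2 (SA3): section 3.7.3 compares Pre-Pain, Pain and Post-Pain, all under in-phase stimulation. There is no CLAS versus no-CLAS contrast to dilute. What suffers is interpretation, because some patients would in effect be observed under pain without CLAS.

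**3. Illustrative size for a Part 1 paired contrast.** All inputs except n = 30 are assumptions: two-sided alpha 0.05, a paired t-test, a standardised effect chosen to give 80% power, and a fraction f of patients with exactly zero effect.

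From the noncentral t with 29 degrees of freedom, 80% power at n = 30 needs dz = 0.529. With the within-group standard deviation of the differences set to 1, the mixture has mean (1 − f)·dz and variance 1 + f(1 − f)·dz², so

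dz_eff = (1 − f)·dz / √(1 + f(1 − f)·dz²)

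For f = 0.10: 0.9 × 0.529 = 0.476; √(1 + 0.09 × 0.280) = 1.013; dz_eff = 0.470.

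| f (assumed) | expected patients of 30 | chance of at least one, 1 − (1 − f)³⁰ | dz_eff | power at n = 30 | n for 80% |
|---|---|---|---|---|---|
| 0 | 0 | – | 0.529 | 80% | 30 |
| 5% | 1.5 | 79% | 0.499 | 75% | 34 |
| 10% | 3 | 96% | 0.470 | 70% | 38 |
| 20% | 6 | 99.9% | 0.414 | 59% | 48 |

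**4. Sensitivity to the starting effect.** At f = 0, 10% and 20%, power is 56, 47 and 39% for dz = 0.4, and 99, 96 and 90% for dz = 0.8. A large true effect would absorb most of the loss.

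**5. Partial loss.** Suppose affected patients keep a share r of the effect. The mean becomes (1 − f(1 − r))·dz and the variance 1 + f(1 − f)(1 − r)²·dz². With f = 20% and r = 0.5 (both assumed): mean 0.9 × 0.529 = 0.476; √(1 + 0.16 × 0.25 × 0.280) = 1.006; dz_eff = 0.474. That is slightly above the 0.470 for 10% with no effect at all, so power stays a little above 70% instead of 59%.

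**The case against.** The strongest reply is that severe loss is already partly filtered and that the rest may matter little. Patients are recruited by a phone call in which the study is explained, which works informally against profound deafness. Enrolment is limited to neurologically healthy patients, which at least partly covers neural and central causes. The sound goes to both ears, so mild or one-sided loss may still leave it audible. All this stands, and it makes an exactly zero effect in a large share of patients an extreme case. It does not cover cochlear or conductive loss. Nor does it cover a hearing-aid user who manages a call but then receives the sound through in-ear earphones.

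Second, section 3.2 time-locks the EEG to sound onset, subtracts sham and identifies early auditory components. Those data could help show whether sound reached the cortex. A reader might infer from the missing criterion that a null result would be impossible to interpret; with these data planned, that goes too far. The article, however, assigns them to separating evoked from ongoing activity and not to checking reception. Section 1.5 also says early auditory cortical responses are suppressed under propofol, so an absent response would not prove that the sound was not transmitted.

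Third, the limitation is disclosed, the bias runs towards the null, and unselected surgical patients are a defensible population for a first study. Disclosure does not deal with the avoidable part, namely loss already known before surgery.

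Fourth, a reader might infer that hearing is neither asked about nor recorded anywhere. A condensed article does not support that: screening scripts and history fields belong to documents not shown. What can be said is that the stated criteria contain no hearing item.

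**Conclusion.** The point holds as a gap between the stated criteria and the article's own premise: a patient with known hearing loss is eligible as written, and patients who do not receive the sound would dilute the Part 1 contrasts. A reader might extend this to every CLAS comparison in the study. SA3 does not support that, because all its epochs are under in-phase stimulation; only its interpretation is affected.

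The size is unknown. The drop from 80% to about 75%, 70% or 59% at 5%, 10% or 20% is illustration only. It rests on an assumed effect size, an assumed prevalence and an all-or-none loss of effect, and partial or one-sided loss would dilute less. It should not be read as a forecast of this trial's power. This is a cheap improvement and not a flaw that undermines the design.

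**What to change.** Preferred: add known significant hearing loss, hearing-aid use or an occluded ear canal to the exclusion list in section 2.1.2, and ask about them in the existing phone screen. If a fuller protocol already contains such a check, stating it in the criteria is enough.

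Minimum alternative, if eligibility is to stay open: record hearing status at screening, and pre-specify the auditory evoked response of section 3.2 as a check of sound reception. Add a sensitivity analysis of the Part 1 contrasts without patients who have known hearing loss or no detectable response. Interpret it with caution, because propofol suppresses early auditory responses and an absent response may reflect the drug and not the ear.

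Cost: one line in the criteria and one screening question, or one recorded item and one additional analysis on data already collected. The exclusion would lose a few older candidates and narrow generalisability slightly.

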#### CLAS algorithm development

2.1.3

Our team has designed a CLAS algorithm for the real-time detection of *δ*-waves, which is directly integrated into an hd-EEG system (128-channel MagstimEGI), using custom Python scripts (Python 3.12.0). Online detection uses a single frontal channel (Fz) sampled at 500 Hz and filtered with a low-pass FIR filter plus moving average to achieve low-latency triggering (20 ms delay). Fz was selected to replicate established CLAS paradigms in sleep (Diep et al., 2021; Dudysová et al., 2024; Navarrete et al., 2020; Ngo et al., 2013; Ong et al., 2016; Papalambros et al., 2017) and because slow oscillations under propofol anesthesia exhibit frontal predominance and preferential involvement of medial cortical regions, with origins and propagation patterns aligned along mesial components of the default mode network (Murphy et al., 2011). For algorithm development and real-time visualization, the CLAS software simultaneously logs 20 additional channels (1–20). Simultaneously, NetStation software (MagstimEGI) acquires the full 128-channel raw EEG for offline analyses.

The CLAS software will deliver one of three types of stimulation: *in-phase*, in the up-slope or up-state of the δ-waves, aiming to be phase-locked with the peak of the δ-waves, *anti-phase*, in the down-slope or down-state of the δ-waves, aiming to be phase-locked with the trough of the δ-waves, and *sham*, where no stimulation happens, as a baseline.

#### δ-wave detection

2.1.4

All δ-waves are defined according to modified version of standard sleep slow waves criteria (Bouchard et al., 2021).

*In-phase*: δ-wave peaks are detected when the following conditions are met: (1) the signal goes below −40 μV; (2) the signal then crosses 0 μV; (3) the difference in amplitude between the minimum (trough) and the current oscillatory activity is greater than 75 μV; and (4) the peak occurs between 500 and 2,000 ms after the detected trough. The auditory stimulation is triggered during the up-slope of the wave, between 270 and 90° (Figure 1). After an auditory stimulation has been triggered, *in-phase* stimulation is deactivated until the filtered signal passes 0 μV again.

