The mechanistic differences between SWs and SOs are directly relevant for interpreting CLAS effects under anesthesia. Whereas SOs primarily index large-scale cortical synchronization and traveling-wave dynamics, SWs reflect the strength and stability of thalamocortical bursting and cortico-thalamic coupling. Consequently, CLAS-induced changes in δ-wave expression may differentially reflect modulation of cortical up–down state timing, thalamocortical engagement, or their interaction, depending on which oscillatory features are most affected.

In the present protocol, SOs and SWs are not separated, and CLAS targets *δ*-waves broadly within the 0.1–4 Hz range. This choice reflects both methodological and physiological considerations. To date, CLAS has not been applied under general anesthesia, and no prior work has established whether SOs and SWs can or should be differentially targeted in this pharmacologically stabilized state. Accordingly, the present protocol targets *δ*-waves to capture the full spectrum of propofol-induced slow activity and maximize sensitivity to stimulation effects in this unexplored context. Nevertheless, distinguishing between these oscillatory components remains conceptually important for interpreting whether CLAS preferentially modulates cortical synchronization, thalamocortical drive, or a combined contribution to general anesthesia unconsciousness.

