**Figure 1 fig1:**
[figure not shown]
Delta-wave degrees. Schematic sinusoidal wave illustrating the phase-based triggering of CLAS. In-phase stimulation is delivered during the up-slope (270–90°), whereas trough stimulation is delivered during the down-slope (90–270°). These directional, phase-specific effects allow CLAS to either enhance (*in-phase*) or disrupt (*anti-phase*) δ-wave expression.

*Anti-phase*: δ-wave troughs are detected when the following conditions are met: (1) the signal goes above 40 μV; (2) the signal then crosses 0 μV; (3) the difference in amplitude between the maximum (peak) and the current oscillatory activity is greater than 75 μV; and (4) the trough occurs between 500 and 2,000 ms after the detected peak. The auditory stimulation is triggered during the down-slope of the wave, between 90 and 270° (Figure 1). To avoid multiple detection within the same slow oscillation, the detection is paused until the filtered signal passes through 0 μV.

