### δ-waves metrics

3.3

Figure 4 illustrates some of the different metrics that are described in the following section. *Amplitude (μV):* The peak-to-peak amplitude was calculated as the absolute difference between the maximum and minimum values of the oscillation: 
$A_{e1-e2}=|V_{e1}-V_{e2}|$
, where *V_e1_* is the value of the first extremum in μV, and *V_e2_* is the value of the second extremum in μV. *Frequency (Hz)*: The mean frequency of the oscillation was defined as the inverse of its duration: 
$F=\frac{1}{d}$
. *Slopes (μV/s)*: We calculated three slope measures to quantify the rate of voltage change within each oscillation: (1) 1st zero-crossing to 1st extremum: 
$\text{slop}e_{\mathrm{zc}[i]\_e1}=\frac{|V_{e1}|}{t_{e1}}$
, (2) 1st extremum to 2nd extremum: 
$\text{slop}e_{e1\_e2}=\frac{A_{p-p}}{|t_{e1}-t_{e2}|}$
, (3) 2nd extremum to last zero-crossing: 
$\text{slop}e_{e2\_\mathrm{zc}[i+1]}=\frac{|V_{e2}|}{d-t_{e2}}$
, where *t_e1_* and *t_e2_* are the time (in seconds, relative to the initial zero-crossing) at which the first and second extremum occur, respectively. *Transition Frequency (Hz):* The transition frequency was defined as the inverse of twice the interval between the first extremum and the second extremum: 
$F_{\text{trans}}=\frac{1}{2|t_{e2}-t_{e1}|}$
. *Density (SOs/s)*: The density of delta waves (*δ*-waves) was defined as the number of δ-waves per second over the full duration of the recording: 
$\text{Density}=\frac{N_{\mathrm{\delta W}}}{T}$
, where *N_δW_* is the total amount of δ-waves detected in the recording, and *T* is the total duration of the recording in seconds.

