#### Effect of CLAS on *δ*-waves morphology and topography

3.7.1

EEG data will be processed at the level of individual channels to characterize the impact of CLAS on δ-wave morphology and topography using custom Python scripts. Each detected δ-wave will be segmented as a single event (250–10,000 ms duration), and morphology will be quantified by amplitude, slope, transition frequency, density, and power spectral density (Bouchard et al., 2021). These metrics will be compared across conditions (*in-phase*, *anti-phase, sham*) and cortical regions of interest (frontal, central, midline, parietal, temporal, occipital). Descriptive statistics will be computed at both the subject and group level, with comparisons assessed using repeated-measures ANOVA and independent-samples *t*-tests, including age and sex as covariates.

Topographical EEG maps will be generated for canonical frequency bands (delta (0.1–4 Hz), theta (4–8 Hz), alpha (8–13 Hz), beta (13–30 Hz)), and phase-amplitude coupling measures will be calculated to further assess condition-dependent differences in oscillatory dynamics. Topographical mapping will allow testing for regional differences, as frontal predominance of *δ*-waves is a hallmark of both sleep and propofol anesthesia (Murphy et al., 2011; Purdon et al., 2015). To extend beyond scalp measures and as an exploratory aim, source estimation will be performed using standardized head models (Michel and He, 2019). Finally, propagation analyses will be conducted to quantify directionality of δ-wave travel across the cortex, as slow oscillations are known to spread as traveling waves and have been proposed as indices of large-scale cortical communication (Massimini et al., 2004; Tononi and Massimini, 2008).

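### The online trigger admits waves of about 0.25-1 Hz, but the protocol says stimulation targets 0.1-4 Hz and scores its outcomes over that whole band

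*Protocol article*

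**What the plan says.** **Trigger.** Section 2.1.4 (δ-wave detection) lists four criteria for each active condition. The fourth in-phase criterion is that "the peak occurs between 500 and 2,000 ms after the detected trough". The anti-phase counterpart is that "the trough occurs between 500 and 2,000 ms after the detected peak". For the in-phase condition, "The auditory stimulation is triggered during the up-slope of the wave, between 270 and 90" degrees.

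**Stated target.** Section 1.5 says: "In the present protocol, SOs and SWs are not separated, and CLAS targets" δ-"waves broadly within the 0.1–4 Hz range". The reason given is "to capture the full spectrum of propofol-induced slow activity and maximize sensitivity to stimulation effects in this unexplored context". Section 1.1 splits the band into slow oscillations below 1 Hz and slow waves of 1-4 Hz. Section 1.8 sets the primary objective for δ-waves of 0.1-4 Hz.

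**Analysis.** In 3.7.1 each detected wave is "segmented as a single event (250–10,000 ms duration"). Section 3.2 bases the primary analyses on individually detected waves, without selecting them by stimulus. In 3.3, "The transition frequency was defined as the inverse of twice the interval between the first extremum and the second extremum"; frequency is the inverse of wave duration.

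**Reach of the effect.** Section 2.2.2 argues that 20-second pauses are enough because stimulation acts only on the cycle it targets.

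**The concern.** The interval from trough to peak, or from peak to trough, is about half a cycle. A rule that demands at least 500 ms for it shuts out fast waves, and a ceiling of 2,000 ms shuts out very slow ones. The waves that can receive a sound are then a subset of the waves the protocol says it targets and of the waves it scores.

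Two things are at stake. The first is interpretation: a result, particularly a null, would be reported as a finding about 0.1-4 Hz activity although most of the 1-4 Hz component was never directly stimulated. The second is sensitivity: if the effect ends with the stimulated cycle, averaging over waves that could not be stimulated pulls per-wave contrasts with sham toward zero.

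**Working it through.** **Inputs.** Extremum-to-extremum interval 500-2,000 ms (2.1.4, both active conditions); stated band 0.1-4 Hz (1.5, 1.8); offline duration 250-10,000 ms (3.7.1); F_trans = 1/(2 × interval) and F = 1/d (3.3).

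**1. The plan's own band.** F = 1/0.25 s = 4 Hz and 1/10 s = 0.1 Hz. The offline window reproduces 0.1-4 Hz exactly.

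**2. The trigger.** F_trans = 1/(2 × 0.5 s) = 1 Hz and 1/(2 × 2 s) = 0.25 Hz. To span 0.1-4 Hz the interval would have to run from 1/(2 × 4) = 125 ms to 1/(2 × 0.1) = 5,000 ms.

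**3. Share of the band.** Linear: (1 − 0.25)/(4 − 0.1) = 0.75/3.9 = 19%. Log: ln(1/0.25)/ln(4/0.1) = ln 4/ln 40 = 38%.

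**4. Asymmetric waves.** If the interval is a share r of wave duration d, then F = 1/d = r/interval.

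| r | F at 2,000 ms | F at 500 ms |
|---|---|---|
| 0.3 | 0.15 Hz | 0.6 Hz |
| 0.5 | 0.25 Hz | 1.0 Hz |
| 0.7 | 0.35 Hz | 1.4 Hz |

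Since r < 1, F always stays below 1/0.5 = 2 Hz. At least (4 − 2)/(4 − 1) = two thirds of the 1-4 Hz band, on a linear scale, is out of reach.

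**5. Another reading of criterion 4.** The sound is given on the up-slope, before the peak has been seen, so the criterion may in practice gate the time from trough to trigger sample. For a sinusoid of 100 µV amplitude, the earliest permitted sample is the zero-crossing, a quarter cycle after the trough: 1/(4f) ≤ 2 s gives f ≥ 0.125 Hz. At 50 µV the 75 µV rise is reached at +25 µV, a third of a cycle after the trough: 1/(3f) ≤ 2 s gives f ≥ 0.167 Hz. The latest up-slope sample is the peak, so 1/(2f) ≥ 0.5 s still gives f ≤ 1 Hz. Running sinusoids of 0.1-4 Hz through the four criteria agreed: under the first reading 0.25-1.0 Hz triggered, and 0.1-0.2 and 1.1-4 Hz never did; under the second the lower limit fell to between 0.125 and 0.2 Hz and the upper limit stayed at 1 Hz.

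**6. Attenuation (illustration only).** Suppose a share s of analysed waves is eligible, ineligible waves do not respond, and the between-subject SD is unchanged. A per-wave mean effect is then multiplied by s. With 30 patients, a paired comparison, two-sided 5% and 80% power, the detectable standardized effect is (1.96 + 0.84)/√30 = 0.51 for s = 1. Dividing by s gives 0.68 (s = 0.75), 1.02 (s = 0.5) and 2.05 (s = 0.25). The documents give no value for s.

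**The case against.** - **The limits are not sharp.** This stands. The 0.25-1 Hz range is strict only for transition frequency or symmetric waves, and the lower edge also depends on how criterion 4 is read. Only the loss at the fast end survives every reading.
- **The size of the attenuation is unknown.** This stands. No distribution of wave frequencies is given, and 2.1.4 refers to modified sleep criteria that may impose an amplitude threshold offline. A simulated spectrum would not fill the gap, because the eligible share would follow from the assumed spectrum, amplitude and threshold.
- **Ineligible waves may still respond.** This partly stands. The Introduction (1.2) describes faster waves nested within slow oscillations, so a stimulated cycle could carry some of them along. Density is a count per second and power spectral density is not a per-wave mean, so simple dilution does not describe either.
- **The all-wave comparison answers the stated objective, and filtering would harm it.** This stands as an argument against replacing the primary metrics. Section 1.8 expects stimulation to change duration, frequency and transition frequency. Selecting waves on the 500-2,000 ms interval conditions on an outcome, and using the same filter in every block does not remove that selection.

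None of this reconciles 1.5 with 2.1.4. The claim to cover the full spectrum remains contradicted.

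**Conclusion.** The contradiction is real and needs no simulation: the trigger corresponds to about 0.25-1 Hz, whereas the stated target and the analysed set are 0.1-4 Hz. No reading lets a wave of 2 Hz or faster trigger a sound. For roughly symmetric waves, the slowest are excluded as well.

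Attenuation of per-wave means such as amplitude and slope is a plausible consequence. It rests on the protocol's premise that effects end with the targeted cycle and on the assumption that ineligible waves do not respond. Its size cannot be computed from the documents.

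A reader might infer three stronger things that the documents do not support:
- That the stated target is not stimulated at all. The 0.25-1 Hz part is.
- That the primary effects shrink by a known fraction. The eligible share is unknown.
- That a planned comparison of slow oscillations with slow waves is invalidated. No such analysis is specified; 1.5 treats the distinction as conceptual.

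**What to change.** Reconcile 1.5, 1.8, 2.1.4 (both conditions) and 3.7.1. Which trigger interval is right is for the investigators to settle.

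**If the trigger window stands:**
- State that stimulation directly targets approximately 0.25-1 Hz activity, withdraw the full-spectrum claim, and limit conclusions, including a null, to that range.
- Keep the all-wave comparison as planned.
- Add a prespecified supporting analysis of trigger-eligible waves, defined by the same offline rule in the in-phase, anti-phase and sham blocks, and report 1-4 Hz waves separately.
- Note that this selection truncates duration, frequency and transition frequency, so those three metrics should be read from the all-wave set.

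**If 0.1-4 Hz is the intended target,** the trigger window must be made consistent with it.

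The first route costs some wording and one offline filter, with no new data. The second also needs a check of the detection software.
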